#### 2.2.1 Exploratory phase.

The exploratory phase will focus on metabolomic analyses to identify the effects of dapagliflozin therapy in humans on the urine composition respectively electrolytes and small molecules that may interfere with the urolithiasis frequency such as oxalate, calcium, magnesium, citrate, and uric acid.

Therefore, one group of 22 participants with a diagnosed cardiomyopathy and/or diabetes Mellitus and indication for dapagliflozin will get a daily oral administration of 10mg dapagliflozin combined with regular blood- and urine test to generate data for the calculation of the effect size. Furthermore, we hope to gain more information about the pharmacologic mechanisms of how dapagliflozin modifies the frequency of urolithiasis events in humans as it has been shown in earlier studies [64,68,69].

The SPIRIT-Study workflow and assessment timeline with primary and secondary endpoints have been presented in Fig 1 and S1. Table.

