#### 2.2.2 Randomized controlled trial.

The second part, the main trial will also be a randomized cross-over single-center study in patients with a high risk of urolithiasis reoccurrence to show if dapagliflozin can modify the urine composition in hyperoxaluric patients with a high stone-forming risk. After a recalculation of the sample size based on the findings of the exploratory phase screenings of potential participants will run to gain the population needed for this trial section.

We hope to demonstrate that dapagliflozin is a new therapy option for high-risk stone formers with no known secondary causes. Participants eligible for the main trial must meet two key criteria: first, they must be selected from a group of patients with similar clinical profiles, specifically those classified as high-risk stone formers who have experienced a significantly increased frequency or severity of urolithiasis events in recent years. Second, they must not have any identifiable secondary causes for these events, such as known metabolic disorders, anatomical abnormalities, or medications known to predispose to stone formation (see 2.4 Trial participants).

After the end of the main trial, the participants of the main trial will be offered to be included in a follow-up trial. The participants will continue to get a daily oral dosage of 10mg dapagliflozin for a period of up to two years. By that, we would like to demonstrate the effect of dapagliflozin on the urolithiasis event rate in humans in the first prospective trial even if short-term or metabolomic data of the first two study phases will gain no new information about the pathophysiology and the pharmacologic pathways behind this disease.

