### 2.4 Trial participants

#### 2.4.1 Trial participants of the exploratory phase.

We plan to include a group of 22 persons in the exploratory phase recruited out of participants suffering from cardiomyopathy and/ or diabetes mellitus. By that, no harm must be feared and especially the diabetic and cardiomyopathy participants will have an indication and a proven benefit of dapagliflozin. Provided that the participants will not suffer any effects pharmaceutical agents that have the potential to interfere with dapagliflozin such as thiazide diuretics, alkaline bicarbonate, bisphosphonate, calcium supplementation, carbonic-anhydrase inhibitors, denosumab, glucocorticoids, loop diuretics, teriparatide, topiramate, xanthin-oxidase inhibitors or 1,25-OH-Vitamin D will be paused four weeks prior of the study to prevent data corruption by through interferences.

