#### 2.6.1 Exploratory phase.

Before the main trial is about to begin there will be an exploratory part of the study. 22 participants with a diagnosis of cardiomyopathy, a given indication for dapagliflozin, and that as well might benefit from the therapy, will be included in one group. For 6 weeks all patients will get an oral therapy of 10mg dapagliflozin daily. To get baseline data of all participants blood and urine samples will be collected before the beginning of the exploratory phase; the treatment response will be evaluated by blood- and urine tests after 4 and 6 weeks of therapy. With the collected data an interim analysis targeting the pathophysiology of urolithiasis as well as the effect mechanism of dapagliflozin will be calculated. Only if the data of the exploratory phase shows a positive effect of dapagliflozin on the excretion rate of oxalate, calcium, phosphate, and uric acid the next part of the main trial will begin.

Patients who already participated in the exploratory phase won’t be treated differently and will have to run through all the following phases whether they already received the trial treatment or not—that way the blinding is still given and whether participants nor investigators can extrapolate their status.

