### 2.7 Ethical concerns/ risk assessment

We plan a prospective pharmacological randomized cross-over single-center study to find out the effectiveness of dapagliflozin in high-risk patients with recurrent kidney stones. The current preventive therapies previously discussed vary widely and have low to zero success rates in many cases. [21,62,63]. The prospective collection and evaluation of blood and urine samples will determine the efficacy of dapagliflozin for this special group of patients. The performance of our study will be according to the principles of the Declaration of Helsinki 2008. The study has received approval from the Institutional Review Board of the Medical University of Vienna (1205/2022).

The planned study procedures in the current prospective observational project are all embedded in the standard of care procedures. At the study visits samples of blood and urine specimens (approx. 60 ml and 9 ml) will be collected to show if dapagliflozin therapy will produce results in this specific group of patients; that do not pose a potential harm to the study participants. However, we assume that no participant will be subjected to any potential harm related to their participation in the study. No interventional procedures will be performed if not clinically indicated. Due to the assumption that dapagliflozin will reduce the oxalate output, there is a probability that participants will experience a significant benefit from the study project. The results from this trial however have the potential of adding significant insight into the efficacy of dapagliflozin therapy in patients with a high risk of recurrent urolithiasis. These results potentially could be highly valuable for future patients in improving their quality of life, kidney function, and kidney stone-related mortality. This study was initially submitted to the EudraCT database under the identifier 2022-000994-13. However, per the regulatory transition requirements, the study has been submitted to the Clinical Trials Information System (CTIS) under the identifier 2024-519371-25-00. This ensures compliance with the latest clinical trial regulation (Regulation (EU) No 536/2014), which mandates the migration of EudraCT studies to CTIS for harmonized trial management and transparency. Both identifiers are provided for reference and traceability.

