#### 2.7.2 Study discontinuation and management of serious adverse events (SAEs).

The study will be discontinued for any participant in the event of a serious adverse event (SAE), significant protocol deviations, or if continuation poses a risk to the participant’s health. Study discontinuation may also occur at the request of the participant or their treating physician. Criteria for discontinuing a participant’s involvement in the study include:

Occurrence of any SAE related to dapagliflozin or placebo that is life-threatening, results in hospitalization, or causes significant disability (diabetic ketoacidosis, severe urinary and genital infections, hypotension, acute kidney injury, fractures, and hypoglycemia).Persistent non-compliance with the study protocol, such as failure to attend required study visits or adhere to the treatment regimen.Development of any new medical condition or complication that contraindicates continued participation, such as a significant decline in renal function (eGFR <15 ml/min/1.73 m²) or other serious medical conditions requiring immediate treatment outside the scope of the study.At the participant’s request, for any reason, or if the participant becomes pregnant during the study period.

In the event of an SAE, immediate steps will be taken to ensure the participant’s safety, including withdrawal from the study treatment if necessary. All SAEs will be reported to the Institutional Review Board (IRB) within 24 hours of awareness, followed by a detailed report within seven days. If necessary, the IRB can recommend study suspension or termination depending on the frequency and severity of the events.

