#### 2.7.3 . Informed consent form (ICF).

Before joining this study, all participants will be asked to review and sign an informed consent form. This process is designed to ensure that each participant:

Understands Why the Study is Being Conducted: Participants will receive clear information about the study’s goals, what we hope to learn, and what participation will involve.Knows Participation is Voluntary: Participation in this study is entirely voluntary. Patients will be reassured that they are free to withdraw at any time without any impact on the quality of their usual medical care.Is Informed About Potential Risks and Benefits: We will explain any potential risks, benefits, or discomforts associated with the study in plain language. Participants will be fully informed about what to expect, including any possible side effects related to treatments being studied.Is Assured of Confidentiality: Participants will be informed of how their information will be kept secure and used strictly for research purposes. Personally identifiable information will remain confidential and protected throughout the study.Has the Chance to Ask Questions: We encourage participants to ask any questions they may have about the study, the procedures, or what their involvement means. Our goal is to ensure they feel comfortable and informed before signing.

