#### WP1. Screening (Pre-study phase, 4 Months).

**Objective:** WP1 includes a prospective analysis of all patients of the Division of Cardiology of the General Hospital of Vienna with a diagnosed cardiomyopathy, diabetes mellitus II and no established SGLT-2 inhibitor therapy. Furthermore, also patients of the Department of Urology of the General Hospital of Vienna with at least one event of urolithiasis and a high risk of reoccurrence will be screened in preparation for the main trial. Baseline data as mentioned earlier of all study participants of the exploratory phase are collected **Methods:** 22 potential study participants fulfilling defined exclusion and inclusion criteria and willing to participate in the exploratory phase will be recruited. Pre-screening of potential participants of the main trial.

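### Section 2.6.1 sends any exploratory participant who enters the main trial through 26 of 34 weeks off a drug the protocol calls indicated, and blinding does not require it

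*Protocol article*

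**What the plan says.** Section 2.2.1 defines the exploratory population as "one group of 22 participants with a diagnosed cardiomyopathy and/or diabetes Mellitus and indication for dapagliflozin", and 2.6.1 repeats that an indication is present. Section 2.4.1 goes further: "By that, no harm must be feared and especially the diabetic and cardiomyopathy participants will have an indication and a proven benefit of dapagliflozin". WP1 selects patients "with a diagnosed cardiomyopathy, diabetes mellitus II and no established SGLT-2 inhibitor therapy", so it is the study that starts the drug. All exploratory participants take 10 mg daily for six weeks in one group.

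For those who then enter the main trial, 2.6.1 states that they are handled like everyone else and "will have to run through all the following phases whether they already received the trial treatment or not". It gives preservation of the blind as the reason.

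Section 2.6.2 and WP4 to WP8 set out the phases: wash-out I, treatment I, wash-out II, treatment II and wash-out III. Group 1 has dapagliflozin in treatment phase I only, group 2 in treatment phase II only. The remaining time is placebo or wash-out.

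**The concern.** The protocol starts an indicated drug in these patients and then fixes a rule under which anyone who continues into the second part is off it for most of that part. The reassurance in 2.4.1 rests on the indication. That argument supports giving the drug for the six exploratory weeks; it does not support withholding it afterwards. Section 2.7 adds a general statement, "we assume that no participant will be subjected to any potential harm related to their participation in the study", which does not mention this group. What is at stake is the treatment of the individual patient and the accuracy of the risk description, not the trial's statistical inference.

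**Working it through.** **Inputs.** Phase weeks come from the headings of WP4 to WP8, counted inclusively. Allocation by period comes from 2.6.2.

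| Phase | Weeks overall | Length | Group 1 | Group 2 |
|---|---|---|---|---|
| Wash-out I | 7–12 | 6 | off | off |
| Treatment I | 13–20 | 8 | on | off |
| Wash-out II | 21–26 | 6 | off | off |
| Treatment II | 27–34 | 8 | off | on |
| Wash-out III | 35–40 | 6 | off | off |

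**Reproducing the plan's own figure.** Main trial = 6 + 8 + 6 + 8 + 6 = 34 weeks. Adding the 6 exploratory weeks gives 40, which matches the stated end in week 40 overall.

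**Time on and off drug, either group.** On = 8 weeks, and 8/34 = 24%. Off = three wash-outs plus one placebo phase = 6 + 6 + 6 + 8 = 26 weeks, and 26/34 = 76%.

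**Longest unbroken stretch off drug.**
- Group 1: wash-out II + placebo phase + wash-out III = 6 + 8 + 6 = 20 weeks (weeks 21–40).
- Group 2: wash-out I + placebo phase + wash-out II = 6 + 8 + 6 = 20 weeks (weeks 7–26).

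WP8 does not say that placebo is given in wash-out III. It is a wash-out from the drug either way, so the count is unchanged.

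**Does blinding need the rule?** In the exploratory phase every participant knowingly receives dapagliflozin, so there is no allocation to hide. In the main trial the blind concerns the sequence of those randomised. A patient who is not randomised has no sequence to reveal. The rule makes sense as a demand for uniform handling of those who do enter; it is no reason to let them enter.

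**Calendar check (3.3.1).** Last planned exploratory entry 01.04.2025 + 6 weeks = 13.05.2025. Main-trial recruitment opens 01.07.2025, which is 49 days later. The direct run from week 6 into week 7 is therefore nominal, and treatment in the interval is not described. The 26 of 34 weeks does not depend on when the main trial starts.

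**The case against.** The strongest reply is that the group may be empty. Section 3.2 recruits exploratory participants through Endocrinology and Cardiology and main-trial participants through Urology. Someone in both would also have to be a high-risk calcium oxalate stone former, and under 2.2.2 "they must not have any identifiable secondary causes for these events, such as known metabolic disorders". This stands as a limit on size. It does not settle the matter: 2.4.3 admits metabolic syndrome, 2.5.5 records diabetes at baseline, cardiomyopathy is not among the exclusions in 2.4.4, and 2.6.1 itself legislates for the overlap.

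Second, nobody is compelled. Under 2.7.2, "Study discontinuation may also occur at the request of the participant or their treating physician", and 2.7.3 tells participants that "they are free to withdraw at any time without any impact on the quality of their usual medical care". Section 2.2.2 also offers dapagliflozin in a follow-up trial. These protections are real. They let an individual leave, or restart the drug after the main trial; they do not change the default for someone who stays.

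Third, the article may simply have left out a provision on continued or rescue treatment that the full protocol contains. That is fair, so no weight is placed on its absence here. The point rests on the rule that is stated.

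Some stronger readings should be resisted:
- A reader might infer that all 22 exploratory participants lose their treatment. The rule reaches only those who enter the main trial.
- A reader might infer that 2.7 is contradicted outright. Its sentence is generic and worded as an assumption, and the no-harm sentence in 2.4.1 belongs to the exploratory phase.
- A reader might express time off drug as a share of the whole 40-week schedule. The calendar gap makes that denominator unreliable.
- A reader might infer measurable clinical harm. The documents give no event rate after stopping dapagliflozin in these patients.

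**Conclusion.** The point holds in a narrow form and is minor. As written, 2.6.1 takes any exploratory participant who enters the main trial through 26 of 34 weeks without a drug that the protocol calls indicated and of proven benefit, with 20 of those weeks unbroken in either sequence. The stated blinding reason does not require it. The week counts are exact, given the phase lengths in the work plan and full passage through the phases. How many patients this concerns is unknown and may be none. No effect on the primary analysis is claimed, and the clinical consequence cannot be quantified from the document.

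**What to change.** Replace the sentence in 2.6.1 with: *Exploratory participants are not eligible for the placebo-controlled main trial; after week 6, continuation of dapagliflozin is decided by the treating physician.* This leaves the phases, the analysis and the eligibility of other Urology patients unchanged, and it does not dictate usual care.

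The cost is that any patient eligible for both parts must be replaced through Urology, where the main trial already recruits. If there are no such patients, the change costs nothing.

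The change has a limit. A stone former with a dapagliflozin indication who is recruited directly through Urology would follow the same 34-week schedule, and this sentence does not address that case.

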#### 2.6.2 Main trial phase.

The main trial will start with wash-out phase I. All patients will receive blood- and 24-hour-urine screenings in week 6 (respectively week 12 overall) to get baseline data. In preparation for the treatment phase I all participants will receive a daily oral placebo administration over the whole period and will be randomized in two groups.

In week 13 the treatment phase I will start and group 1 will receive oral therapy with 10mg of dapagliflozin while group 2 will get an oral placebo administration daily; the treatment response will be evaluated by blood- and urine test after 4 weeks of therapy (respectively week 16 overall) and in the beginning of in washout phase II (respectively week 21 overall). The same test as before will be performed after 6 weeks (respectively week 26 overall) to gain baseline data for treatment phase II. In preparation for the treatment phase II, all participants will receive a daily oral placebo administration. will receive a daily oral placebo administration.

In the end, we will perform treatment phase II with an oral administration of 10mg of dapagliflozin for group 2 and daily placebos for group 1. The treatment response will be evaluated by blood- and urine tests after 4 weeks of therapy (respectively week 30 overall). Finally, the same tests as before will be performed in wash-out phase III in weeks 1 and 6 (respectively weeks 35 and 40 overall). This way we will get data of the non-therapy periods and of the outcome that will be caused by the dapagliflozin therapy. For each patient, a comparison will be made between the excretion of the electrolytes and molecules of the primary and secondary endpoints under dapagliflozin therapy vs. oral placebo administration.

Throughout the whole study procedure, all participants will be advised to follow dietary instructions as recommended in the urolithiasis guidelines of 2023 [62]. The requested measures will include a balanced diet including a high ratio of vegetables and fibers, a low-fat diet, a calcium intake of about 1.0 to 1.2g per day, a reduced intake of salt up to a maximum of 4.0 to 5.0g per day and an intake of animal proteins of 0.8 to 1.0g per kg per day may reduce stone development risk. Furthermore, patients are strongly advised to not lose or gain weight tremendously throughout the trial process so that the date will be comparable over the whole trial period.

By that measure the investigators want to create a comparable environment for all participants that will lead to comparable data once between the data of one participant over the whole trial period and secondly between all participants independently of their individual dietary habits. In combination with a longer observation period variability should be reduced and the gained data will show a realistic representation.

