**Methods:**

This study will proceed in two phases: an exploratory phase and a randomized controlled phase. In the exploratory phase, 22 participants with indications for dapagliflozin treatment will be evaluated before and after treatment initiation to ascertain the concrete effect size regarding oxalate and calcium-sparing effects. This data will inform the calculation of the study sample size (ranging from 17 to 104 participants) to include high-risk calcium oxalate kidney stone formers in a randomized controlled crossover study design. Treatment phases—one with dapagliflozin and one with placebo—will alternate with wash-out phases involving placebo. The primary outcome is the reduction of oxalate excretion in 24-hour urine samples compared to baseline values after 8 weeks of therapy. Secondary objectives include analysing effects on kidney function, the frequency of urolithiasis, and treatment tolerance. Additionally, in-depth metabolomics analyses will explore pathophysiological pathways during treatment. Investigators, patients, and research staff will be blinded to the randomization list. This study was initially registered under EudraCT (Nr:2022-000994-13) and has been transitioned to CTIS (Nr: 2024-519371-25-00) to comply with EU Regulation 536/2014, ensuring streamlined management and transparency.

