#### 2.5.3 Primary endpoint of the main trial.

As the primary endpoint, we chose *the reduction of the urine oxalate excretion after 8 weeks of dapagliflozin therapy* compared to the baseline value that was collected in the washout phase before the treatment period.

As a secondary objective, we chose to compare the oxalate and calcium-sparing effects such as the kidney function, the frequency of urolithiasis events within the study period, and the tolerance to each treatment. The rationale behind this is a combination of two findings: 1) the reduced urolithiasis event rate under SGLT-2 inhibitor therapy in former trials [68, 69] and 2) the reduced oxalate excretion in a rat model about the effect of SGLT-2 inhibitors on urolithiasis [69]. Further, AstraZeneca holds a patent for the use of SGLT-2 inhibitors to prevent and treat kidney stones [81].

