#### WP5. Treatment phase I (week 13–20).

**Objective** dapagliflozin therapy or placebo administration. **Methods:** all patients will receive an oral dose of 10mg of dapagliflozin or oral placebo daily according to their randomization; blood- and 24h-urine screenings in week 4 (respectively week 16 overall).

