#### WP6. Wash-out phase II (weeks 21–26).

**Objective** Wash out of the pharmacologic agent used in treatment phase I and estimate treatment response. **Methods:** The same blood and 24h-urine screenings as before will be performed in wash-out phase II in weeks 1 and 6 (respectively weeks 21 and 26 overall). Daily placebo administration in preparation for treatment phase II.

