#### WP8. Wash-out phase III (weeks 35–40).

**Objective** Wash-out of the pharmacologic agent used in treatment phase II and estimating treatment response. **Methods:** The same blood and 24h-urine screenings as before will be performed in wash-out phase III in weeks 1 and 6 (respectively weeks 35 and 40 overall).

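### The urine that must serve as the 8-week primary value is scheduled in week 1 of the wash-out, with no day fixed relative to the last treatment-phase dose

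*Protocol article*

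**What the plan says.** **Endpoint.** Section 2.5.3 sets the primary endpoint as "the reduction of the urine oxalate excretion after 8 weeks of dapagliflozin therapy", against a baseline from the preceding wash-out. The abstract agrees ("reduction of oxalate excretion in 24-hour urine samples compared to baseline values after 8 weeks of therapy"), and WP9 repeats the 8-week time point.

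**Schedule.** The first treatment phase is headed "WP5. Treatment phase I (week 13–20"; WP7 gives weeks 27 to 34 for the second. WP5 lists one collection, "blood- and 24h-urine screenings in week 4 (respectively week 16 overall", and WP7 lists one at week 30, also treatment week 4. Section 2.6.2 describes the first period's response samples as "after 4 weeks of therapy (respectively week 16 overall) and in the beginning of in washout phase II (respectively week 21 overall".

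**Wash-outs.** WP6 says the next tests "will be performed in wash-out phase II in weeks 1 and 6 (respectively weeks 21 and 26 overall", and WP8 places the last ones in "wash-out phase III in weeks 1 and 6 (respectively weeks 35 and 40 overall". During wash-out II patients take placebo: "Daily placebo administration in preparation for treatment phase II". WP8 does not name a treatment for wash-out III; only the abstract's general statement that wash-outs involve placebo covers it. WP6 and WP8 each give the phase two purposes: clearing the drug and estimating the response to it.

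**The concern.** A sample meant to show the effect of 8 weeks of treatment should be taken while that treatment is still being given. Here the two samples that must carry the primary endpoint sit in a phase whose purpose is to remove the drug, and how long after the last treatment-phase dose they are taken is left open.

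If urinary oxalate starts to return to its untreated level once dapagliflozin stops, the dapagliflozin value drifts towards the placebo value. The difference shrinks, by an amount that depends on the day each patient happens to collect. A real effect could be missed, and the result could not be reported as an 8-week on-treatment effect. Both treatment orders are exposed: group 1 has its dapagliflozin response sample at week 21, group 2 at week 35.

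There is also a mismatch with planning. The exploratory phase samples after 4 and 6 weeks of a 6-week course (section 2.6.1), so the main trial's sample size would rest on an on-treatment effect while its primary test might use an off-treatment one.

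**Working it through.** **Step 1: place each urine in its phase** (sections 2.6.2 and WP4 to WP8).

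| Overall week | Phase | Position |
|---|---|---|
| 12 | Wash-out I | week 6, baseline |
| 16 | Treatment I (13–20) | treatment week 4 |
| 21 | Wash-out II (21–26) | week 1 |
| 26 | Wash-out II | week 6, baseline |
| 30 | Treatment II (27–34) | treatment week 4 |
| 35 | Wash-out III (35–40) | week 1 |
| 40 | Wash-out III | week 6 |

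That is seven urines, which matches the seven time points listed for the secondary endpoints in section 2.5.4. The text therefore has no urine in treatment weeks 5 to 8 (overall weeks 17–20 and 31–34).

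**Step 2: reproduce the plan's own figure.** Inputs from the 25% row of Table 1 and section 2.3.1: means 1.0 and 1.25, SDs 0.20 and 0.25, correlation 0.1, paired t-test, 90% power.

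- SD of the difference = √(0.20² + 0.25² − 2 × 0.1 × 0.20 × 0.25) = √0.0925 = 0.304
- Standardised effect = 0.25 / 0.304 = 0.822
- With n = 18, noncentrality = 0.822 × √18 = 3.49 on 17 degrees of freedom
- Power at two-sided 0.05 = 90.7%, and 18 is the smallest n reaching 90%, as Table 1 states

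Sections 2.3.1 and 2.3.2 also state a significance level of 0.025. At that level power with 18 patients is 83.7%, and 21 would be needed. The illustration below uses 0.05 because that level reproduces the table.

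**Step 3: illustrate the possible loss.** The documents do not say how fast a urinary effect fades after stopping. Assume it fades exponentially with half-life h days. The share retained at t days is 2^(−t/h). For collection spread evenly over days 1 to 7, take the mean of that share over the seven days. Multiply 0.25 by the share, keep the SD of the difference at 0.304 and n at 18, and recompute power at two-sided 0.05.

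| Collection | h = 1 day | h = 3 days | h = 7 days |
|---|---|---|---|
| No loss | 100% kept, power 91% | 100% kept, power 91% | 100% kept, power 91% |
| One day after stopping | 50% kept, power 38% | 79% kept, power 74% | 91% kept, power 85% |
| Evenly over days 1–7 | 14% kept, power 8% | 44% kept, power 31% | 69% kept, power 62% |

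For example, with h = 3 and day 1: 2^(−1/3) = 0.794; 0.25 × 0.794 = 0.198; 0.198 / 0.304 = 0.652; power 74%.

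**The case against.** A reader might infer that the endpoint is never measured on 8 weeks of dapagliflozin, or that every primary sample follows the switch to placebo. The text does not go that far. Section 2.6.2 speaks of the beginning of wash-out II without giving a day. The first day of week 21 is also the first day after eight completed weeks of treatment, so a urine finished then could largely reflect the last treatment-phase dose. Section 2.6.2 and WP6 show that this sample was intended to capture treatment response. Figures 1 and 2 and the S1 Table are not shown and may fix the day. For week 35, placebo rests on the abstract's general wording alone.

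A reader might also take the power figures as this trial's actual loss. They are not. The half-lives are assumed, and the choice of collection day matters as much as the half-life. The 18 patients belong to the exploratory phase; the main trial's size is to be recalculated, with 17 to 104 participants given in the abstract. And 0.05 is only one of two stated significance levels.

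These points stand, and they limit what can be said about the size of the bias. They do not remove the inconsistency: section 2.6.2 and WP5 to WP8 agree with one another, so the wash-out label is not an isolated slip. The week-16 and week-30 urines do give an on-treatment comparison, but at 4 weeks; using them would change the stated endpoint.

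**Conclusion.** The point holds as an inconsistency between endpoint and schedule. The endpoint is defined after 8 weeks of therapy; the last urine inside a treatment phase is at 4 weeks; and the sample that must stand for 8 weeks is labelled wash-out week 1, with its timing relative to the last treatment-phase dose left open. This follows from the protocol's own week numbers and needs no assumption.

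The consequence is conditional. If the urine is completed on the first day, little or nothing may be lost. If it is taken later, any reversible effect is diluted towards no difference. Under the stated assumptions power ranges from 91% down to about 8%; this shows that the collection day can matter greatly, and it is not an estimate for this trial.

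It should be settled before the main trial starts, because it concerns the only confirmatory endpoint and cannot be repaired once the urines have been collected.

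**What to change.** Reconcile section 2.5.3 with section 2.6.2 and WP5 to WP8. Move the two urines now at weeks 21 and 35 to the last days of weeks 20 and 34, while the period's assigned study medication is still being taken, and name them as the primary 8-week values. Bring the figures and the S1 Table into line if they differ.

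The cost is a short amendment that shifts two existing collections by days. There are still seven urines, with no additional visits or patients, and dosing is unchanged.
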